**Methods/Design:**

This is a double-blind randomised controlled trial. Adult smokers attending a 7-session weekly stop smoking clinic will be randomised to either a modified visual probe task with attentional retraining or placebo training. Training will start 1 week prior to quit day and be given weekly for 5 sessions. Both groups will receive 21 mg transdermal nicotine patches for 8–12 weeks and withdrawal-orientated behavioural support for 7 sessions. Primary outcome measures are the change in attentional bias reaction time and urge to smoke on the Mood and Physical Symptoms Scale at 4 weeks post-quit. Secondary outcome measures include differences in withdrawal, time to first lapse and prolonged abstinence at 4 weeks post-quit, which will be biochemically validated at each clinic visit. Follow-up will take place at 8 weeks, 3 months and 6 months post-quit.

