### Trial procedures

Participants in both trial arms will be seen weekly in clinics from 2 weeks prior to quit day up to 4 weeks post quit day. There are ten clinic sessions in total. Randomisation takes place at the second clinic session, which initiates the first of the 5 weekly AR/PT sessions. Follow up visits take place at 8 weeks and 3 months post quit day, with a final visit arranged at 6 months. Participants will be paid £15 to complete assessments at 3 month and 6 month follow-up sessions, as these are not therapeutic encounters. Participants will be reminded to attend their appointments by telephone or text message. Staff will complete a case report form (CRF) at each clinic visit, which contains a checklist of the trial procedures.

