### Measures

Table 1 displays the treatment and measurement plan for the study. The measures consist of the following:

• A baseline questionnaire to collect information on the demographic and clinical characteristics of participants. Participant age, gender, ethnicity, education and employment status are classified using UK Census 2011 categories [40]. The questionnaire also contains information on smoking history including the Fagerström Test of Nicotine Dependence (FTND) [41], a 6-item measure assessing the severity of nicotine dependence.

• A visual probe task and pictorial Stroop task to assess attentional bias.

• The Mood and Physical Symptoms Scale (MPSS) [42]. This will be administered at the beginning of every session to assess urge to smoke and withdrawal. A modified version of the MPSS will be used in which each of the nine items is rated on a scale from 1–7. Items relating to the strength and frequency of urges can be combined to produce a composite score (MPSS-C); this is also the case for combined mood items (MPSS-M). The MPSS was preferred over other measures such as the Questionnaire of Smoking Urges because of its superiority in predicting treatment outcomes [43,44].

• Exhaled carbon monoxide (CO). Readings will be taken at the beginning of each session to biochemically verify smoking status.

• A visual analogue scale (VAS) to measure cue-induced craving at the beginning of the second session and following attentional bias assessments. Measurements will be recorded on a 100 mm scale from “Not At All” to “Extremely” prior to and after the task.

• Ecological Momentary Assessment (EMA) [45] to collect information on lapses. EMA is an approach to collecting data in real-time on hand-held electronic devices; it does not carry the risk of recall bias like paper diaries [46]. Participants will be given an electronic diary at the first session and they will be instructed to record any lapses that occur and the circumstances in which the lapse occurs up to 5 weeks post quit day. Those who use an electronic diary will be paid up to £75 at the 8-week session for completing assessments in this way.

• A questionnaire on knowledge of group allocation.

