### Primary trial outcomes

• Measure of attentional bias during assessment trials of the visual probe task, as measured by the difference in median reaction time (ms) taken to respond to probes replacing smoking-related stimuli versus probes replacing neutral stimuli. This will be assessed at 4 weeks post-quit in abstinent and non-abstinent smokers across both trial arms, following recommendations of Shiffman et al. [60].

• Strength of weekly urge to smoke on the MPSS, measured up to 4 weeks post-quit in abstinent and non-abstinent smokers across both trial arms.

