### Analysis

• Primary analyses

• Attentional bias scores on the visual probe task will be calculated by subtracting median RTs to probes that replace smoking-related pictures from median RTs to probes that replace neutral pictures, with positive scores indicating a bias towards smoking cues and negative scores indicating a bias towards neutral cues. Median RTs will be used because distributions of mean RTs are often reported as skewed [33,63]; therefore we do not need to set parameters for outlying RTs. Bias scores, as measured at 4 weeks post-quit, will be used to examine AR effects on attentional bias firstly by trial arm and secondly by abstinence status using ANCOVA. An alpha level of 0.05 will be used. These analyses will be performed using PASW Statistics 18 (SPSS, Inc., 2009, Chicago, IL, USA).

• To investigate AR effects on weekly urge to smoke, data will be analysed using a mixed effects regression model with an autoregressive variance-covariance structure, to allow for variations in craving between participants. This will enable all weekly time points to be included and modelled simultaneously. An autoregressive modelling structure takes into consideration that repeated craving measurements taken closer together in time on the same participant are likely to be more highly correlated than measurements that are taken further apart in time [64]. This modelling technique will be used for MPSS composite scores for urge to smoke (MPSS-C). Regression coefficients, p-values and 95% confidence intervals (CI) will be derived from the models. These analyses will be undertaken using Stata 12.0 (StataCorp, 2011, College Station, TX: StataCorp LP).

• Intention-to-treat analyses will be performed to account for people who drop out of treatment.

• Secondary analyses

• Effects of AR on withdrawal will be examined using the same technique stated for urge to smoke analyses, in a mixed effects regression model of composite scores for withdrawal symptoms (MPSS-M). We will control for baseline MPSS-M scores, as is standard for the MPSS [42].

• To determine the proportion of people achieving abstinence by trial arm, risk ratios (RRs) will be calculated with corresponding 95% CIs. Those reported as lost-to-follow up will be counted as non-abstinent, as is standard in the reporting of smoking cessation trials [39,65].

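### The primary urge outcome is a week 4 value in the abstract but a weekly series in the body, and no first outcome visit is fixed

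*Protocol article*

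**What the plan says.** The protocol article places the primary urge outcome in three sections.

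- Abstract, Methods/Design: "urge to smoke on the Mood and Physical Symptoms Scale at 4 weeks post-quit". This is a single time point.
- Primary trial outcomes: "Strength of weekly urge to smoke on the MPSS, measured up to 4 weeks post-quit". This is a weekly series with an end but no start.
- Analysis, primary analyses: "data will be analysed using a mixed effects regression model with an autoregressive variance-covariance structure", applied to MPSS-C, with the reason given that "This will enable all weekly time points to be included and modelled simultaneously".

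The schedule determines what the weekly time points could cover. The section on procedures gives the visits as follows: "Participants in both trial arms will be seen weekly in clinics from 2 weeks prior to quit day up to 4 weeks post quit day". Measures, on the MPSS: "This will be administered at the beginning of every session to assess urge to smoke and withdrawal". Randomisation and the first training session take place at the second visit, week -1.

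Baseline handling differs between sections. The secondary analysis of withdrawal (MPSS-M) adjusts for the baseline score. The primary analysis of MPSS-C has no such statement. The power calculation for urge adjusts for quit-day urge, with a correlation of 0.41.

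The other primary outcome, attentional bias, is placed at 4 weeks post-quit in all three sections, so the conflict concerns urge only.

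**The concern.** A week 4 value and a weekly series are different primary quantities. If the training effect builds up over the five sessions, or fades once withdrawal has peaked, the two can give different answers from the same data. As written, a week 4 result, a post-quit average or an average over all weekly visits could each be reported as the primary result after the data have been seen.

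The missing first visit adds to this. Read with the visit schedule, all weekly time points would run from week -2 to week +4. The first two of those ratings are made before any training, so randomisation makes the expected arm difference zero there. The third, on quit day, follows one session and precedes the first post-quit week. Study question 2 asks about urges during cessation. An arm effect averaged over such visits would be smaller than the effect in question.

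**Working it through.** **1. Which ratings follow which training.** Training is given at weeks -1, 0, +1, +2 and +3, and the MPSS is rated at the start of each visit.

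| Visit | Sessions completed before the rating |
|---|---|
| -2 | 0 |
| -1 | 0 |
| 0 (quit day) | 1 |
| +1 | 2 |
| +2 | 3 |
| +3 | 4 |
| +4 | 5 |

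**2. The plan's own figure.** Inputs from the power calculation: difference 0.6, SD 1.2, power 80%, type 1 error 5% (two-sided assumed). The formula is n per group = 2(1.96 + 0.8416)² × SD² / difference².

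- Unadjusted: 2 × 7.849 × 1.44 / 0.36 = 62.8, which rounds up to 63 (stated: 62).
- Adjusted for quit-day urge: 62.8 × (1 - 0.41²) = 62.8 × 0.8319 = 52.2, which rounds up to 53 (stated: 53).

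The stated sample size is therefore reproduced. It treats quit-day urge as an adjustment value, not as an outcome.

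**3. Size of the dilution if it occurs.** This step makes two assumptions that the protocol does not state: all seven visits are outcomes, and one constant arm term is estimated over them. Under AR(1) with correlation ρ, the generalised least squares weights are proportional to 1 for the first and last visits and to 1 - ρ for those between. The share of the true effect that is recovered is then:

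- effect from week +1: [1 + 3(1 - ρ)] / [2 + 5(1 - ρ)]
- effect from quit day: [1 + 4(1 - ρ)] / [2 + 5(1 - ρ)]

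For example, at ρ = 0.41 with the effect from week +1: 2.77 / 4.95 = 0.560, and 0.560 × 0.6 = 0.336. The protocol gives no visit-to-visit correlation for this model, so a range is shown.

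| ρ (assumed) | Effect from week +1 | Effect from quit day |
|---|---|---|
| 0 | 0.343 | 0.429 |
| 0.41 | 0.336 | 0.407 |
| 0.6 | 0.330 | 0.390 |
| 0.8 | 0.320 | 0.360 |

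With weeks +1 to +4 as the only outcome visits, and a constant effect over them, the estimate stays at 0.60.

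**4. Power at 53 per group** (normal approximation, SD 1.2, no baseline covariate). The standard error is 1.2 × √[(2/53) × (1 + ρ) / (2 + (T - 2)(1 - ρ))] for T visits.

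| Outcome visits | ρ = 0.41 | ρ = 0.6 | ρ = 0.8 |
|---|---|---|---|
| Weeks +1 to +4 | 97% | 93% | 84% |
| All seven, effect from quit day | 91% | 75% | 51% |
| All seven, effect from week +1 | 77% | 61% | 43% |
| Week +4 only | 73% | 73% | 73% |

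**5. When there is no dilution.** An arm-by-visit term, a week +4 contrast, or a model that takes the pre-training ratings as baseline leaves the post-training contrasts at 0.60. One qualification concerns quit day. If it stays in as an outcome and the effect begins only at week +1, a pooled term over weeks 0 to +4 recovers [1 + 3(1 - ρ)] / [2 + 3(1 - ρ)]. That gives 0.48 at ρ = 0 and 0.44 at ρ = 0.41.

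**The case against.** A reader might infer that the planned model does include the pre-training ratings and does shrink the effect, so that a real benefit could be lost. The documents do not support that.

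No sentence says that weeks -2 and -1 are outcome visits; the remark about all weekly time points explains why a mixed model was chosen. Several places suggest a post-quit window:

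- The outcome is to be measured in abstinent and non-abstinent smokers, a distinction that has meaning only after quit day.
- The power calculation refers to the first 4 weeks and uses quit-day urge for adjustment.
- The withdrawal model uses the same technique with baseline as a covariate.
- The study question concerns cessation.

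Nor does the protocol specify a single arm term pooled over visits. The exact model terms may properly be left to an analysis plan that is not shown here.

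A zero effect on quit day is also not a given, because one session has been completed by then. Loss of power is not certain either. Repeated ratings reduce variance, and at a correlation of 0.41 even the diluted seven-visit analysis has 77% to 91% power, against 73% for an unadjusted week 4 comparison.

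All of this stands, and it makes the dilution conditional. It does not remove the conflict between the abstract and the body, or the absence of a first outcome visit. Both concern stated text on a primary outcome.

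**Conclusion.** The primary urge outcome is defined in two incompatible ways, as a week 4 value and as a weekly series whose first visit is not given. That is certain from the text and should be corrected.

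The numerical consequence is conditional. It requires the week -2, week -1 and quit-day ratings to be entered as outcomes and one arm term to be pooled over all seven visits. A true 0.6-point effect would then be estimated at roughly 53% to 57% of its size if it begins at week +1, or 60% to 71% if it begins on quit day. These shares rest on assumed AR(1) correlations of 0 to 0.8 and on an effect that is constant once it has begun. It would go too far to say that the plan as written dilutes its primary effect or will miss a real one.

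Baseline handling is part of the same point. Adjustment is stated for MPSS-M but not for MPSS-C, while the reduction from 62 to 53 per group depends on an urge covariate, and that covariate is rated after the first training session.

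**What to change.** State one primary urge estimand in the same terms in the abstract, Primary trial outcomes and Analysis. One suitable choice is the arm difference in MPSS-C over weeks +1 to +4, with the week +4 contrast from the same model reported as supportive, since week +4 is the only weekly rating made after all five sessions. Name the arm contrast explicitly.

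Use a pre-training rating as a baseline covariate and not as an outcome, in line with the baseline adjustment already stated for MPSS-M. Reconcile this with the power calculation, which adjusts for quit-day urge. Conditioning on a value rated after one session could absorb part of an early effect. The 0.41 correlation is between quit-day and post-training urge and may not hold for an earlier rating, so the 53 per group should be rechecked or its basis stated.

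The cost is wording in these sections and a check of the sample-size covariate; no new data are needed. The downside is that an average over weeks +1 to +4 still mixes ratings made after two, three, four and five sessions, which is why the week +4 contrast should accompany it.

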### Ethics and research governance

The trial will be conducted in compliance with the principles of the Declaration of Helsinki (1996), the ICH-GCP, the EU Clinical Trials Directive and all applicable regulatory requirements. The study protocol and other documentation were approved by the National Research Ethics Committee (10/H1206/34) and local NHS Research & Development offices. Subsequent protocol amendments will be submitted to the Research Ethics Committee for approval, and the other bodies where necessary. We will provide the Research Ethics Committee with annual progress reports, in addition to a final study report.

## Discussion

This is the first trial to assess the potential clinical translation of AR procedures in smokers attempting to quit using NHS SSS. Multiple sessions of AR might increase treatment efficacy on top of standard treatment, as demonstrated in a recent trial of alcohol-dependent patients [33]. If effective, not only could AR be used in stop smoking clinics, it could also be offered as a web-based intervention on NHS stop smoking websites as another potentially low-cost alternative.

Several procedures are in place to minimise potential sources of bias. To minimise the risk of selection bias, we are using a simple random sequence for assigning participants to groups. To minimise performance bias, we are blinding all therapists and participants to group allocation, though there is a risk of participants becoming aware of which group they have been assigned to while carrying out the task itself. At follow up, we will assess participants’ knowledge of which intervention they believe to have received.

While this trial offers the ability to examine AR as a therapeutic tool, data on attentional bias and its relation to urges to smoke, cue-induced cravings and resumption of smoking will enhance our understanding of relapse and possible preventative strategies. Knowing how urges to smoke strike, their antecedents and smoker’s responses to these are a key part of designing future intervention strategies.
